## Materials and methods

2

This is a single-center randomized, double-blind, prospective, controlled trial with 21 days of follow-up. A revised version of the manuscript has been submitted, and SPIRIT-Checklist and SPIRIT-Figure. The project was submitted to the Research Ethics Committee (REC) of the Universidade Nove de Julho – UNINOVE and approved (#3505689). After verbal and written explanation of the study, participants who agree to participate in the study will sign an Informed Consent Form (ICF) and a Terms of Assent (TA) for children between 10–18 years of age, the person responsible for applying the therm will be the researcher ([name]). The study will be conducted in accordance with the *Declaration of Helsinki* (revised in Fortaleza, 2013). The Project was registered at www.clinicaltrial.gov (NCT 04037709). The patients will come from three centers located in Brazil: Dellê Dentistry – [name]; Odontocorpus Dentistry and Health – [name]; and [name] and Team Clinic– [name], from July 2019 to December 2021. There is no conflict of interest regarding the clinics where the research will be conducted. Project receive grant from Brazilian National Coordination for the Improvement of Higher Education Personnel CAPES # 1690040 (CAPES Portuguese: Coordenação de Aperfeiçoamento de Pessoal de Nível Superior (CAPES). Any intercurrence will be notified to the REC and reported in the publication. If necessary, the study will be ended before the stated date. In addition, if evaluations of the dosimetric parameters for the laser, as described in the initial protocol, show that the results are not adequate, the protocol may be adjusted. The sample will be composed of patients who have used a fixed appliance for at least 12 months and with gingivitis present, detailed description in the sample. The experimental design will consist of 2 groups (described in detail in Experimental Design). Samples will be collected for microbiological evaluation and measurement of inflammatory cytokines in the crevicular fluid and saliva. Periodontal clinical data will be collected for diagnosis of gingivitis and for comparison of these parameters after 7 and 21 days to check for improvements. The Oral Health Impact Profile Questionnaire (OHIP-14) questionnaire will also be applied to measure the quality of life related to oral health.

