### Study variables

2.13

The primary study variable will be

GI as determined using a periodontal probe at baseline (T_0_), 7 (T_1_) and 21 (T_2_) days after treatment.

The secondary variables of the study will be:

Clinical PD at baseline (T_0_), 7 (T_1_) and 21 (T_2_) days after treatment;Visible PI at baseline (T_0_), 7 (T_1_) and 21 (T_2_) days after treatment;GI at baseline (T_0_), 7 (T_1_) and 21 (T_2_) days after treatment.Oral health-related quality of life (OHRQoL) will be assessed using the OHIP-14 questionnaire at baseline (T_0_) and 21 (T_2_) days after treatment;Evaluation of cytokines IL-6, IL-1β, IL-8, TNF-α and IL-10, by ELISA method, in non-stimulated saliva and crevicular fluid at baseline (T_0_), 7 (T_1_) and 21 (T_2_) days after treatment;Microbiological analysis by means of the *Universal bacteria* count (16S rRNA gene) present in crevicular fluid (sites with hyperplasia), and non-stimulated saliva at baseline (T_0_), 7 (T_1_) and 21 (T_2_) days after treatment.

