### Statistical analysis

2.15

Statistical analysis will be performed using only the data obtained from patients who have completed the study. If the sample is normally distributed, Student's T test will be used to compare the means of the continuous and dependent variables. If the distribution is not normal, the Mann-Whitney test will be used. Data will be presented by their means ± SD and the p value will be set at 0.05. All tests will be performed using GraphPad Prism 5 (GraphPad Software, San Diego, USA). The significance level will be set at *p* < 0.05.

Spreadsheets with the survey data will be stored in their own space during the survey. To avoid duplicate data entry, only one researcher will be responsible for entering the data into the spreadsheets for further statistical analysis. The responsible is [name].

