The randomization of the participants according to the two proposed groups will be followed by the double blinding of the study. The researcher responsible for data collection, the microbiologist and the statistician will be blind to the treatments; the patient will also be blind to the type of treatment performed. We will use the double-blind study methodology to prevent any intentional or unintentional interference with the results of the experiment.

All participants will receive oral hygiene treatment and guidance on the first day of the study. The choice of a single treatment session aims to verify its feasibility in clinical practice, given that orthodontic maintenance is usually performed monthly. Reevaluation after 7 and 21 days will be important to determine if the reduction in inflammation was maintained.

The choice to treat the most contaminated sites rather than the mouth is based on consideration of the oral cavity homeostasis, in which the focus is not on having a totally decontaminated cavity but to have the punctual and local resolution of the inflammation in places difficult to access. To maintain said equilibrium, it is preferably the pseudo-pockets which will be treated with PDT.

The methodology will be determined by a diagnostic and analytical triad: clinical, microbiological and biomarker analysis, considering clinical practice as the most important. We will also evaluate the patient's quality of life as gingival inflammation may cause painful symptoms, loss of function and aesthetic alterations, all or any of which may decrease the patient's quality of life.

In the study by Zanatta et al, 2012,^[39]^ the OHIP14 questionnaire was used to check the quality of life of patients who had gingivitis during fixed orthodontic treatment. It was noticed that there was a greater impact when the patients had anterior gingival enlargement. Thus it was concluded that by preventing and treating gingivitis and anterior gingival enlargement while still undergoing orthodontic treatment, the patient's quality of life could be improved. The OHIP 14 is also the questionnaire of choice for our quality of life assessment.

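### The plan asks questions about change over time in the same patients, but names no paired or repeated-measures method, and its fallback, Mann-Whitney, ignores pairing if used within an arm

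*Protocol article*

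**What the plan says.** Section 2.13 (Study variables) defines the primary variable as "GI as determined using a periodontal probe at baseline (T_0_), 7 (T_1_) and 21 (T_2_) days after treatment". Probing depth, plaque index, cytokines and bacterial counts follow the same three visits; OHIP-14 is taken at T0 and T2 only.

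Two places give a purpose that concerns time. Section 2 (Materials and methods) says that the clinical data serve diagnosis and "for comparison of these parameters after 7 and 21 days to check for improvements". The Discussion adds: "Reevaluation after 7 and 21 days will be important to determine if the reduction in inflammation was maintained".

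Section 2.15 (Statistical analysis) assigns the tests. With a normal distribution, "Student's T test will be used to compare the means of the continuous and dependent variables". Otherwise, "If the distribution is not normal, the Mann-Whitney test will be used". The abstract repeats this pair. Neither place says whether the t test is paired, and neither names a signed-rank, Friedman, repeated-measures or mixed-model method. The threshold is the usual 0.05, with sidedness not stated.

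**The concern.** A question about improvement or maintenance compares readings from the same people. Mann-Whitney is a test for two independent samples and has no paired form. Section 2.15 makes no exception for comparisons over time. An analyst who follows it literally for day 7 against day 21 within one arm would treat 17 patients read twice as 34 unrelated people. An unpaired t test would do the same.

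The non-normal branch may well be reached. GI is a percentage of bleeding sites, bounded at 0 and 100, and the other outcomes include qPCR counts and cytokine levels, which are often skewed. With 17 patients per arm, little protects against that.

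At stake is the quality of the within-arm statements on improvement and durability. Repeat readings are normally positively correlated. Ignoring the correlation overstates the standard error, so the test rejects too rarely and real changes between visits are harder to see.

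**Working it through.** **Inputs from the article.** 17 patients per arm (sections 2.1 and 2.10); significance level 0.05 (section 2.15); three visits in the same patients (section 2.13).

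**Assumptions, because the article gives no figure.** Two-sided testing; within-patient correlation rho of 0.3, 0.5 or 0.7; a change between two visits of 0.4, 0.5 or 0.8 SD; bivariate normal readings with equal SD. The 0.40 in section 2.1 is an effect size for bacterial counts between arms, so using 0.4 SD for a change over time only borrows the figure.

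**The plan's own figure.** It states no error rate or power for a comparison over time, so there is nothing to reproduce.

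**Standard errors, in SD units, n = 17.**
- Unpaired: sqrt(2/n) = sqrt(2/17) = 0.343, whatever the correlation.
- True value for the difference between two visits: sqrt(2(1 − rho)/n). This is 0.287 at rho 0.3, 0.243 at rho 0.5 and 0.188 at rho 0.7.
- Ratio of true to assumed: sqrt(1 − rho) = 0.84, 0.71 and 0.55.

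The unpaired test therefore works with a standard error that is too large by a factor of 1.2 to 1.8.

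**Simulated rejection rates**, one arm, visit against visit (20,000 runs per setting; 4,000 for Mann-Whitney). Each cell gives unpaired t / Mann-Whitney / paired t.

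| rho | No change (type I error) | 0.4 SD | 0.5 SD | 0.8 SD |
|---|---|---|---|---|
| 0.3 | 2.0 / 1.9 / 5.0% | 17 / 15 / 26% | 26 / 25 / 38% | 64 / 61 / 75% |
| 0.5 | 0.8 / 0.9 / 5.0% | 13 / 12 / 34% | 23 / 23 / 50% | 66 / 62 / 88% |
| 0.7 | 0.1 / 0.2 / 5.0% | 9 / 8 / 51% | 19 / 18 / 70% | 69 / 65 / 98% |

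**Check of one cell.** At rho 0.5 and 0.5 SD the paired t test has noncentrality 0.5/0.243 = 2.06 on 16 degrees of freedom, which gives power 49%; the simulated 50% agrees within simulation error. In a separate run at the same setting, Mann-Whitney reached 22% and the Wilcoxon signed-rank test 45%, so the rank tests show the same gap.

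**Between-arm control.** With no true difference and 17 per arm, the unpaired t test of G1 against G2 rejected in 4.6% to 5.2% of runs at a single visit, and in 4.6% to 4.9% on within-patient change. Both are close to the nominal 5%.

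**The case against.** The main case on the other side is that the trial's question is between arms. The hypothesis in the Introduction and the sample size in section 2.1 both compare PDT with control, and both named tests serve that comparison, including a comparison of each patient's change from day 7 to day 21. Section 2.15 nowhere says that visits will be compared within an arm by an unpaired test. The sentence in section 2 could describe comparing arms at each visit, and the one in the Discussion explains the visit schedule. A condensed article may also leave detail to a fuller document.

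Much of this stands. The randomised contrast is not in doubt, and it would be wrong to say that the non-normal branch can give no valid test involving time: Mann-Whitney on change scores between arms is valid. Nor can one say that both named tests are independent-samples tests, because Student's t has a paired form and the article does not say which is meant.

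A reader might also infer that a relapse between day 7 and day 21 would probably be missed and then reported as a maintained reduction. The article does not support that. It has no rule that treats a non-significant result as maintenance. Whether a relapse is missed depends on its size and on the correlation: at 0.8 SD the unpaired t test still detects 64% to 69% over rho 0.3 to 0.7. At 0.4 SD and rho 0.5 the paired t test itself misses about 65%, so the small sample matters as well as the choice of test.

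What the objection does not remove is that the article states purposes concerning time and gives a definite test rule without limiting it to comparisons between arms. In the non-normal branch, that rule has no suitable form for a comparison of visits within an arm. This goes beyond detail left to another document.

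**Conclusion.** The point holds for within-arm comparisons over time. If section 2.15 is applied to them as written, Mann-Whitney (and Student's t if taken as unpaired) ignores the pairing and is too conservative. With 17 patients the actual type I error is about 2% at rho 0.3, 0.8% at rho 0.5 and 0.1% at rho 0.7, against a nominal 5%. Power for a 0.5 SD change at rho 0.5 is about 23%, against 49% for the paired t test.

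These sizes rest on assumed correlations and changes and on normal data. The direction needs only a positive correlation between repeat readings. Comparisons of G1 with G2, at a visit or on change, are not affected. The revision is worth making before analysis because it is nearly free, but it does not threaten the main result.

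**What to change.** In section 2.15:

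- Restrict the unpaired Student's t test and Mann-Whitney to G1 against G2, at a visit or on within-patient change.
- For comparisons over time, name a paired t test or Wilcoxon signed-rank test on within-patient differences, or a mixed model with arm, visit, arm-by-visit and a random patient effect.
- Address maintenance by reporting the T1-to-T2 change with its 95% confidence interval in each arm, and the between-arm difference in that change.
- Label within-arm results as descriptive, so that any claim for PDT rests on the between-arm contrast.

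The cost is a few sentences and slightly more analysis, with no new data or patients. The paired and signed-rank tests are standard; a mixed model may need software other than the package named in section 2.15.

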## Abstract

It is known that the presence of orthodontic brackets predisposes for a change in the biofilm, facilitating the development of gingivits. The sites are difficult to access with a toothbrush and periodontal curette, worsening inflammation, in addition, a gingival hyperplasia is associated with poor hygiene. The objective of this study is to evaluate the impact of photodinamyc therapy (PDT) as an adjuvant treatment, considering clinical immunoregulatory and microbiological parameters. This randomized, controlled, double-blind clinical study will include 34 patients, both genders, having used fixed appliance for more than 12 months, with gingivitis. Participants will be divided into two groups: G1 (n = 17)- Scaling and Root Planing + PDT placebo and G2 (n = 17)- Scaling and Root Planing + PDT. In G2 the following dosimetric parameters will be used: methylene blue 0.005%, λ= 660 nanometers (nm), 9 Joules (J) per site, irradiance= 3.5Watts (W)/ centimeters (cm), radiant exposure= 318J/cm^2^. All participants will receive oral hygiene guidance prior the curetes scaling. The clinical periodontal data to be analyzed are plaque index, gingival index and probing depth. Crevicular fluid, from 4 pre-determined sites and saliva, will be collected and analysed for IL-6, IL-1β, IL-8, TNF-α and IL-10 cytokines using ELISA (Enzyme immunoabsorption assay) method. Total *Bacteria* count will also be performed, by qPCR and *Universal16SrRNA* gene. All analysis will be realized using in the baseline (T_0_), 7 (T_1_) and 21 (T_2_) days after treatment. Oral health-related quality of life will be assessed using the OHIP-14 questionnaire at times T_0_ and T_2_. If sample distribution is normal, the Student T-test will be applied if it is not normal, the Mann-Whitney test will be used. The data will be presented in terms of ± PD and The significance level will be set at p < 0.05. Our results may improve quality of life and add data to establish a therapeutic alternative for gingivitis during the orthodontic treatment. Registration: clinicaltrials.gov NCT04037709. https://clinicaltrials.gov/ct2/show/NCT04037709 - Registered in July 2019.

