### Experimental design

2.10

Immediately prior to periodontal treatment, the investigator will remove and open 1 envelope (without changing the numerical sequence of the other envelopes) and perform the indicated procedure. In this manner, the 34 patients will be allocated into the experimental or control groups, as follows:

**G1**- Control group (n = 17) - patients will receive scaling and oral hygiene guidance + application of placebo PDT.

**G2**- Experimental group (n = 17) - patients will be treated with scaling and oral hygiene guidance + PDT application. Photodynamic therapy will be performed at 8 sites with gingival hyperplasia (pseudopocket).

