**Table 2 T2:**

Sequences and references for primers used.

To determine the number of plasmid copies/ μl, necessary to assemble the qPCR curve, it will be estimated that 1 μg of 100 bp of DNA would be equivalent to 9x10^11^ plasmids. These will then be serially diluted, and the curve will comprise 10 to 10^8^ plasmids, which will then be compared to the DNA of the analyzed samples. The number of *Universal Bacteria* will be calculated assuming 1 copy of the 16S rRNA gene/ chromosome.^[37]^ As a negative control sterile Milli-Q water will be added instead of DNA to the template.

Quantitative analysis will be performed by comparing the results obtained with the samples to the data obtained with the standard curve. For the quantification of *Universal Bacteria* 16S rRNA in saliva and biofilm samples, species-specific primers (5 ’CCATGAAGTCGGAATCGCTAG 3” and 5’ GCTTGACGGGCGGTGT 3’) will be used.^[37]^ The reaction will be realized with a total volume of 10 μL containing 5 μL of SYBR Green, 2 μL of sample and 200 μM of each primer for 16S rRNA. Cyclization will be performed: 95°C / 10 min holding, 40 cycles at 95°C / 15 s, 60°C / 1 min, melting curve 95° C / 15 s, 60°C / 1 min (+0.6°C collection) and 95^o^C / 15 s. Only those reactions in which the efficiency was 100% (+ or - 10) R^2^ near to 1 will be considered.

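### Section 2.15 fixes mean ± SD as the summary even when the rank test is used, so skewed bacterial counts and cytokines would be described by means that the test does not compare

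*Protocol article*

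**What the plan says.** Section 2.15 (Statistical analysis) chooses the test by distribution. For normal data: "If the sample is normally distributed, Student's T test will be used to compare the means of the continuous and dependent variables". Otherwise: "If the distribution is not normal, the Mann-Whitney test will be used". The sentence that follows sets the summary with no condition on either branch: "Data will be presented by their means ± SD and the p value will be set at 0.05". The Abstract is equally unconditional: "The data will be presented in terms of ± PD and The significance level will be set at p < 0.05", where the abbreviation after the plus-minus sign appears to stand for the standard deviation.

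The outcomes most exposed are secondary variables in section 2.13. One is the 16S rRNA count in crevicular fluid and saliva ("Microbiological analysis by means of the *Universal bacteria* count (16S rRNA gene) present in crevicular fluid (sites with hyperplasia"). The others are five cytokines in two fluids ("Evaluation of cytokines IL-6, IL-1β, IL-8, TNF-α and IL-10, by ELISA method, in non-stimulated saliva and crevicular fluid"), which makes 5 × 2 = 10 measures. No section mentions a median, an interquartile range, a geometric mean or a log scale for them. Section 2.1 sizes the trial on the difference in bacterial quantity in crevicular fluid, so the count matters more than its secondary status suggests. Section 2.10 gives the group size: "Control group (n = 17) - patients will receive scaling", with 17 also in the PDT group.

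**The concern.** The plan foresees non-normal data and changes the test, but not the summary. Mann-Whitney asks whether values in one arm tend to rank above those in the other. A difference in arithmetic means is another quantity, and with skewed data the two can disagree. At 17 per arm a raw mean of a skewed concentration can depend on one or two high values. The SD can then exceed the mean, so that mean minus SD is negative for a quantity that cannot be negative.

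What is at stake is the effect as readers will see it. With groups this small, some of the many secondary comparisons may well be non-significant. Readers then fall back on the descriptive figures to judge size and direction, and there mean ± SD is least stable.

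**Working it through.** The plan states no figure to reproduce. The check is what its reporting rule would produce.

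**Inputs from the protocol article:** 17 per arm (section 2.10); significance level 0.05, taken as two-sided (section 2.15); Mann-Whitney for non-normal data (section 2.15); counts and cytokines with no transformation stated (sections 2.13 and 2.14.5).

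**Assumed, because the documents give no spread:** log-normal values, log10 SD (σ) of 0.3, 0.5, 0.7 and 1.0, summaries on the raw scale, and a true PDT effect of 0.5 log10. Normality is judged by Shapiro-Wilk, since the article names no test.

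**Method:** simulation of 20,000 trials per scenario. For log means the chance of the wrong direction also has a closed form: Φ(−0.5 / (σ·√(2/17))), with √(2/17) = 0.343. This gives Φ(−4.86) ≈ 0%, Φ(−2.92) = 0.2%, Φ(−2.08) = 1.9% and Φ(−1.46) = 7.2%.

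| Assumed σ (log10) | 0.3 | 0.5 | 0.7 | 1.0 |
|---|---|---|---|---|
| Median of sample SD / mean | 0.7 | 1.1 | 1.6 | 2.1 |
| Arms with SD above the mean | 7% | 67% | 94% | 99% |
| Trials with normality rejected in at least one arm | 88% | >99% | ≈100% | ≈100% |
| Raw means point the wrong way, all trials | 0% | 1% | 8% | 19% |
| Log means point the wrong way, all trials | 0% | 0.2% | 2% | 7% |
| Raw means oppose a significant Mann-Whitney result | 0% | 0.2% | 2% | 5% |

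**Dominance by a few patients:** the two largest of 17 values hold a median 28% of the arm total at σ = 0.3, 41% at 0.5 and 69% at 1.0. With identical arms, the ratio of raw means has a 95% range of 0.59 to 1.68 at σ = 0.3, 0.37 to 2.73 at 0.5 and 0.07 to 14.2 at 1.0.

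**Power:** at σ = 0.7, Mann-Whitney has about 50% and a t test on logs about 53%.

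**Upper limit on SD/mean:** the log-normal population ratio is √(exp(s²) − 1) with s = σ·ln 10. It is 1.7 at σ = 0.5 and 14 at σ = 1.0. A sample of 17 non-negative values cannot show more than √17 = 4.1, which is reached only when one value is positive and the rest are zero. The table's medians of 0.7 to 2.1 are what a report of this trial would show.

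**The case against.** The strongest reply is that this concerns descriptive reporting of secondary outcomes, in a condensed article, with skewness that the documents never show. Much of that stands, and it rules out several stronger readings.

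- **That the qPCR curve shows how skewed patients are.** Section 2.14.5.4 says "the curve will comprise 10 to 10^8^ plasmids". That is the calibration range of the assay, not the spread between patients. At σ = 0.3 the SD stays below the mean in 93% of arms, and the harm is slight.
- **That the tests lose validity or power.** A t test on raw values would do badly here (about 22% power at σ = 0.7), but the plan sends non-normal data to Mann-Whitney, which keeps nearly all the power of a log analysis.
- **That the reported direction will often contradict the test.** Raw means oppose a significant rank result in at most about 5% of such trials. The larger figures of 8% and 19% cover all trials, including non-significant ones.
- **That no effect estimate or interval will be produced.** The article does not say so. It is silent, and an analysis plan may supply them.
- **That medians cure instability of direction.** With the same 0.5 log10 effect, medians also point the wrong way in about 1%, 4 to 5% and 12% of trials at σ = 0.5, 0.7 and 1.0. Most of the gain comes from the log scale; the median's merit is that it suits a rank test better.

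The appeal to an unseen analysis plan does not remove the core point. The article does not leave the summary open. It fixes mean ± SD straight after allowing a rank test, and the Abstract repeats it.

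**Conclusion.** The point holds as a flaw in reporting and effect description for bacterial counts and cytokines. The mismatch between summary and test is written in section 2.15; its size is conditional. It rests on log-normal data, summaries on the raw scale and an assumed spread. It is mild at a log10 SD of 0.3 and clear from about 0.5 upward, where the SD exceeds the mean in two thirds of arms or more and log means point the wrong way much less often than raw means.

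It does not reach the p values, the sample size or the significance level. The primary variable, the gingival index, is a percentage bounded at 0 and 100 and is less affected, although the same unconditional rule covers it. The change is worth making because the count is the quantity on which section 2.1 sizes the trial.

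**What to change.** In section 2.15, and in the matching sentence of the Abstract:

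1. Analyse bacterial counts and cytokines as log10 values. Report geometric means by arm and the PDT/control ratio with a 95% CI.
2. For any other outcome tested by Mann-Whitney, replace mean ± SD with median (IQR) and give the Hodges-Lehmann difference with a 95% CI. Keep mean ± SD where the t test on the untransformed scale is used.
3. State before unblinding how values below the detection limit will be substituted, since zeros and undetected values have no logarithm.

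The cost is wording and a transformation. No extra data, visits or participants are needed, and the significance level is unchanged. The small downside is that results for counts and cytokines are read as ratios, and the substitution rule adds one choice that must be fixed in advance.
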